5.1 Efficacy and safety evaluation

### 5.1.1 Classification of treatment outcomes

Artesunate should produce parasite reduction ratios of approximately 10,000/cycle, which result in parasite clearance times, which are usually less than 48 hours. This is a descriptive study; its purpose will be a detailed analysis of how the group responds.

Treatment outcomes will be classified on the basis of an assessment of the parasitological and clinical outcome of antimalarial treatment according to the latest WHO guidelines.[[1]](#footnote-2) Thus, all patients will be classified as having early treatment failure, late clinical failure, late parasitological failure or an adequate clinical and parasitological response, as defined in Appendix 4.

As parasitological cure is the goal of antimalarial therapy, all study patients who show treatment failure will be given rescue treatment. Follow-up will continue until recovery. The results from these patients do not need to be recorded systematically for the purpose of the surveillance study.

### 5.1.2 Safety end-points

The number of any adverse event will be documented. All patients will be asked routinely about previous symptoms and about symptoms that have emerged since the previous follow-up visit. When clinically indicated, patients will be evaluated and treated appropriately. All adverse events will be recorded on the case report form. Serious adverse events (see definitions in 5.3) must be reported to the sponsor with 48 hours.

5.2 Clinical evaluation

All patients will be evaluated clinically as described below.

### 5.2.1 Physical examination

A standard physical examination will be performed at baseline (day 0 before dosing) and on days 1, 2, 3, 7, 14, 21, and 28. A complete medical history, demographic information and contact details will be taken at baseline.

### 5.2.2 Body weight

Body weight will be recorded on day 0 to the nearest kilogram on a Salter scale. The scales will be properly calibrated. Patients should not wear excessive clothing while being weighed as this can overestimate their true weight. The screening weight will be used to satisfy the inclusion or exclusion for nutrition status as well as to calculate the dose (number of tablets) to be administered. The reliability of the scales will be verified before the study begins and checked at regular intervals.

### 5.2.3 Body temperature

Axillary, oral temperature will be measured at baseline (day 0 before dosing) and on days 1, 2, 3, 7, 14, 21, and 28. Temperature will be measured with a thermometer that has a precision of 0.1 °C. Temperature will also be measured as clinically indicated. If the result is < 36.0 °C, the measurement will be repeated. The same route should be used throughout the study.

The quality of the temperature-taking technique and the thermometers should be assessed regularly. Thermometers should be tested in a water-bath of known temperature before the study begins and at regular intervals thereafter.

### 5.2.4 Microscopic blood examination

Thick and thin blood films for parasite counts will be obtained and examined at screening on day 0 to confirm adherence to the inclusion and exclusion criteria. Thick or thin blood films will be also examined every 12 hours until PCT and on days 1, 2, 3, 4, until negativation, 7 (if after PCT), 14, 21, 28 or on any other day if the patient returns spontaneously and parasitological reassessment is required. Specimens will be labelled anonymously (screening number or study number, day of follow-up, date).

A fresh Giemsa stain dilution will be prepared at least once a day and possibly more often, depending on the number of slides to be processed. Giemsa-stained thick and thin blood films will be examined at a magnification of 1000 to identify the parasite species and to determine the parasite density.

Three blood slides per patient will be obtained: two thick blood smears and one thin blood smear. One slide will then be stained rapidly (10% Giemsa for 10–15 min) for initial screening, while the others will be retained. If the patient is subsequently enrolled, the second slide will be stained more carefully (e.g. 2.5–3% Giemsa for 45–60 min), and slower staining will also be used for all slides obtained at follow-up visits. The study number of the patient, the date and the day of follow-up will be recorded either on the frosted edge of the slide or on the glass with a permanent glass pen.

The thick blood smear for initial screening will be used to count the numbers of asexual parasites and white blood cells in a limited number of microscopic fields. The adequate parasitaemia for enrolment is at least one parasite for every six white blood cells, corresponding to approximately 1000 asexual parasites per microlitre.

The second blood smear will be used to calculate the parasite density, by counting the number of asexual parasites in a set number of white blood cells (typically 200) with a hand tally counter. Once a field has been started, it must be counted to completion; the final number of white blood cells will therefore rarely be exactly 200. If more than 500 parasites have been counted before 200 white blood cells have been reached, the count will be stopped after the reading of the last field has been completed. Parasite density, expressed as the number of asexual parasites per µl of blood, will be calculated by dividing the number of asexual parasites by the number of white blood cells counted and then multiplying by an assumed white blood cell density (typically 6000 per µl).

|  | Parasite density (per µl) = number of parasites counted  (6000) |  |
| --- | --- | --- |
|  | Number of leukocytes counted |  |

The same technique will be used to establish the parasite count on each subsequent blood film. When the number of asexual parasites is less than 10 per 200 white blood cells in follow-up smears, counting will be done against at least 500 white blood cells (i.e. to completion of the field in which the 500th white blood cell is counted). A blood slide will be considered negative when examination of 1000 white blood cells reveals no asexual parasites. The presence of gametocytes on an enrolment or follow-up slide will be noted, but this information will not contribute to basic evaluation.

In addition, 100 fields of the second thick film will be examined to exclude mixed infections; in case of any doubt, the thin film will be examined for confirmation. If examination of the thin film is not conclusive, the patient will be excluded from the analysis after complete treatment and follow-up.

Two qualified microscopists will read all the slides independently, and parasite densities will be calculated by averaging the two counts. Blood smears with discordant results (differences between the two microscopists in species diagnosis, in parasite density of > 50% or in the presence of parasites) will be re-examined by a third, independent microscopist, and parasite density will be calculated by averaging the two closest counts.

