3.5 Inclusion criteria

- age > 18 years;
- mono-infection with *P. falciparum* detected by microscopy;
- parasitaemia of 10 000-100 000/µl asexual forms;
- presence of axillary ≥ 37.5 °C or oral or history of fever during the past 24 h;
- ability to swallow oral medication;
- ability and willingness to comply with the study protocol for the duration of the study and to comply with the study visit schedule; and

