Appendix 5. Case screening form

**.**

**.**

| **Case screening form** | | | | | |
| --- | --- | --- | --- | --- | --- |
| Health centre name: | | | | | Study number: |
| Locality: | | | | | Patient screening number: |
| District: | | | | | Date of visit (dd-mmm-yyyy): |
| Province: | | | | |  |
| **Demographic data** | | | | | |
| Date of birth (dd-mmm-yyyy): | | | or estimated age:       in:  months or  years | | |
| Height (cm): | Weight (kg): | |  | | |
| Sex:  Male  Female | | |
| If female, is the patient pregnant?  Yes  No  Not sure | | | | | |
| If pregnant, provide the date of the last menstrual period (dd-mmm-yyyy): | | | | | |
| **Pre-treatment temperature** | | | | | |
| History of fever in previous 24 h?  Yes  No | | | | | |
| Temperature:       ºC  Axillary  Tympanic  Rectal  Oral | | | | | |
| **Thick and thin blood smears for estimation of *P. falciparum*****parasite counts** | | | | | |
| Species:  *P. falciparum*  *P. vivax*  *P. ovale*  *P. malariae* | | | | | |
| Were species other than *P. falciparum* present?  Yes  No **(If yes, patient is not eligible).** | | | | | |
| Approximate number of *P. falciparum* asexual parasites:  Presence of 10–100 parasites / 6 white blood cells?  Yes  No **(If no, patient is not eligible)** | | | | | |
| Presence of *P. falciparum* gametocytes?  Yes  No | | | | | |
| Has a blood sample for PCR been collected?  Yes  No | | | | | |
| Haemoglobin:       g/dl | | Haematocrit:       % | | | |
| **Urinary analysis (pregnancy test for female patients)** | | | | | |
| Result of pregnancy test:  Positive  Negative **(If positive, patient is not eligible)** | | | | | |
| **Inclusion criteria** | | | | | |
| - age > 18years - mono-infection with *P. falciparum* confirmed by positive blood smear (i.e. no mixed infection) - parasitaemia between 10000 and 100000/µl of asexual forms - measured temperature (depending on method of measurement) or history of fever within previous 24 h - ability to swallow oral medication - ability and willingness to comply with the study protocol for the duration of the study and to comply with the study visit schedule - absence of severe malnutrition (defined as per protocol) | | | | | |
| Does the patient meet all the inclusion criteria?  Yes  No **(If no, patient is not eligible)** | | | | | |
| **Case screening form (page 2)** | | | | | |
| **Exclusion criteria** | | | | | |

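### Section 5.2.4 gives a screening parasitaemia threshold of about 1000/µl, ten times below the lower inclusion limit in section 3.5 and on the screening form

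*Protocol*

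**What the plan says.** The protocol states the parasite density needed for enrolment in four places.

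- Section 3.5, inclusion criteria: "parasitaemia of 10 000-100 000/µl asexual forms".
- Appendix 5, inclusion list on the screening form: "parasitaemia between 10000 and 100000/µl of asexual forms".
- Appendix 5, rapid-smear question on the same form: "Presence of 10–100 parasites / 6 white blood cells". A negative answer makes the patient ineligible.
- Section 5.2.4, instruction for the screening smear: "The adequate parasitaemia for enrolment is at least one parasite for every six white blood cells, corresponding to approximately 1000 asexual parasites per microlitre". No upper limit is given.

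Section 5.2.4 also fixes how a cell ratio becomes a density, by "multiplying by an assumed white blood cell density (typically 6000 per µl"), and when a slide is negative: "A blood slide will be considered negative when examination of 1000 white blood cells reveals no asexual parasites". The rapidly stained slide is used for screening. The second slide, which gives the formal density, is stained carefully only for patients who go on to be enrolled.

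**The concern.** Three of the four statements agree and one does not. The odd one out is the instruction addressed to the person reading the smear on which enrolment is decided. The formal count from the second slide comes after that decision.

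Two consequences are possible if staff follow 5.2.4.

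- **The error is found.** Section 3.8 treats a patient who did not meet the inclusion criteria as an erroneous inclusion: withdrawn, no treatment outcome assigned, and censored or excluded from the analysis. Section 8.1 sets a minimum of 40 patients and a target of 50, so the sample has little to spare.
- **The patient is kept.** PCT is part of the primary objective (section 2). Day-3 positivity is a listed end-point (section 5) and the basis of the sample size (section 8.1). Both depend on the starting count as well as on the rate of clearance. A patient who starts below 10,000/µl reaches the detection limit sooner at the same rate, so these two measures would look better than in the intended population.

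**Working it through.** **1. Converting the ratios.** By section 5.2.4, density = parasites ÷ white cells counted × 6000.

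| Source | Parasites per 6 white cells | Density per µl |
|---|---|---|
| Section 5.2.4 | at least 1 | 1/6 × 6000 = 1000 |
| Screening form, lower end | 10 | 10/6 × 6000 = 10,000 |
| Screening form, upper end | 100 | 100/6 × 6000 = 100,000 |

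The figure of about 1000 in 5.2.4 reproduces from its own ratio, so the sentence is consistent within itself and is not a garbled number. The form matches section 3.5 at both ends. The discrepancy at the lower limit is 10,000 ÷ 1000 = 10.

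**2. Effect on day-3 positivity, if low-density patients are enrolled and kept.** Assumptions: log-linear clearance without a lag, and positivity judged at 72 h. The detection limit follows from the negative-slide rule: 1 ÷ 1000 × 6000 = 6/µl.

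For starting density N, the slide is still positive at 72 h only if the half-life exceeds 72 × ln 2 ÷ ln(N/6). Equivalently, the 48 h reduction ratio must be below (N/6)^(2/3).

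| N per µl | N/6 | Half-life needed | 48 h reduction ratio below |
|---|---|---|---|
| 1000 | 166.7 | 9.8 h | about 30 |
| 10,000 | 1666.7 | 6.7 h | about 141 |
| 100,000 | 16,666.7 | 5.1 h | about 653 |

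**3. Effect on PCT.** A tenfold lower start saves log2(10) = 3.32 half-lives. Section 5.1.1 says "Artesunate should produce parasite reduction ratios of approximately 10,000/cycle". Taking a cycle as 48 h (assumption), the half-life is 48 × ln 2 ÷ ln 10,000 = 3.61 h, and the saving is 3.32 × 3.61 = 12.0 h. At an assumed half-life of 6 h it is 3.32 × 6 = 19.9 h. Films are taken every 12 hours, so the first figure is one sampling interval.

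**4. Who is affected.** At a 10,000-fold fall per 48 h, the fall over 72 h is 10,000^1.5 = 1,000,000-fold. Even 100,000/µl then drops to 0.1/µl, below the detection limit. Starting density changes day-3 status only in slow-clearing infections.

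**5. Chance of day-3 positivity, illustration only.** The protocol gives no distribution of half-lives. Assume they are log-normal with log-SD 0.2 to 0.6, with the median set so that the 15% of section 8.1 applies at 31,600/µl, the geometric middle of the range, where the needed half-life is 5.82 h. With log-SD 0.4 the median is 5.82 ÷ exp(1.036 × 0.4) = 3.85 h. From 1000/µl, ln(9.76/3.85) ÷ 0.4 = 2.33, a chance of 1.0%. From 10,000/µl, ln(6.73/3.85) ÷ 0.4 = 1.40, a chance of 8.1%. Over the whole range of log-SD the chances are about 0 to 3% and 4 to 10%. Moving the reference density between 10,000 and 100,000/µl gives 0 to 5% at 1000/µl.

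**The case against.** The strongest reply is that the protocol already blocks these patients.

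- Section 5.2.4 itself says the day-0 films serve to confirm the inclusion criteria, so it defers to section 3.5.
- Section 6.1 makes the Appendix 5 form the screening record and asks for consent only after all criteria are met.
- That form carries the right rule in the microscopist's own units, with a stop, and then repeats the density range with a second stop.
- After enrolment, two microscopists count the second slide, and section 3.8 removes anyone found ineligible.

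All of this stands. Nothing in the document shows how often these checks would fail. The two harms are also largely alternatives: if section 3.8 is applied, the cost is lost patients, for which section 8.1 already adds 20%; bias arises only if it is not applied.

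A reader might infer that the trial will admit patients who can hardly be day-3 positive, and so will hide artemisinin resistance. The document does not support that. Low-density patients enter only if staff override the form. The low chance of positivity depends on an assumed spread of half-lives, and even an eligible patient at 10,000/µl has only a modest chance on the same assumptions. Sections 5 and 8.2 also include the slope of the log-linear clearance curve, which under this model does not depend on the starting count. Finally, because 5.2.4 has no upper limit, it would also pass smears above 100 per six white cells, which would shift PCT and day-3 positivity the other way.

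What the reply does not remove is the contradiction, or the fact that the wrong figure sits in the instruction for the smear that decides enrolment.

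**Conclusion.** The point holds as an internal inconsistency. Section 5.2.4 is wrong as written, by exactly a factor of ten at the lower limit and by omission at the upper limit, measured against section 3.5 and two lines of the screening form. That part rests only on the protocol's own conversion.

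The consequence is conditional. It needs staff to follow 5.2.4 in place of the form, and then either costs patients from a target of 50 or, if low-density patients are retained, biases PCT and day-3 positivity downward. The sizes (9.8 h against 6.7 h for day-3 positivity; 12 to 20 h in PCT) rest on log-linear decay, a 6/µl detection limit, a 48 h cycle and an illustrative 6 h half-life. This should be corrected before enrolment, but given the safeguards it does not put the design in question and is not a must-fix.

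**What to change.** Reconcile section 5.2.4 with section 3.5 and Appendix 5 by replacing the threshold sentence with wording such as: *Parasitaemia is adequate for enrolment when the screening smear shows 10 to 100 parasites per six white blood cells, corresponding to approximately 10,000-100,000 asexual parasites per microlitre.* This states both limits in the units used at the microscope.

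The cost is one sentence, agreed through the amendment route in section 8.4 if the protocol has already been accepted. The eligibility criterion, the form, the sample size and the analysis do not change.

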### 5.2.5 Genotyping of falciparum parasites

In order to differentiate a recrudescence (same parasite strain) from a newly acquired infection (different parasite strain), a genotype analysis will be conducted. This is based on the extensive genetic diversity among the malaria parasite genes *msp1*, *msp2* and *glurp*.[[2]](#footnote-3) The genotypic profiles of pre- and post-parasite strains are compared.

In order to minimize discomfort to the patient due to repeated finger pricks, two to three drops of blood will be collected on filter paper Whatman 3MM during enrolment and each time blood smears are required according to the protocol on and after day 7.

Specimens will be labelled anonymously (study number, day of follow-up, date), kept in individual plastic bags with desiccant pouches and protected from light, humidity and extreme temperature until analysed. When these conditions cannot be achieved, for example in extremely humid environments where air-conditioning is not available, storage in a refrigerator or freezer may be considered, but great care must be taken to protect samples from frost and moisture. The techniques used are polymerase chain reaction, PCR-RFLP and sequencing. The tests will be done at the laboratory of Department of Medical Research, lower Myanmar. Paired filter papers will be used for parasite DNA extraction and genotyping only in cases of treatment failure. Unused filter papers will be destroyed immediately after the study.

### 5.2.6 Molecular markers for antimalarial drug resistance

*P. falciparum* isolates will be collected for whole-genome sequencing. The samples will be genotyped for close to one million SNPs (single nucleotide polymorphisms) and will contribute to creating an overall picture of fine-scale global genetic variation of *P. falciparum*. This project is designed to uncover unique genetic signatures present in the Myanmar *P. falciparum* parasite population.

At admission to the trial, a single blood sample of 5 ml will be collected into EDTA tubes. Host white blood cells will be removed using a Lymphoprep (Axis-Shield) separation and PlasmodiPur filtration (Eurodiagnostika, The Netherlands) step. The parasite DNA will be extracted using DNA Blood Maxi Kits (QIAGEN). Blood samples will be transported to the Wellcome Trust to the Mahidol Oxford Research Unit in Bangkok and will be shipped to the Wellcome Trust Sanger Institute, UK at the end of the clinical trial.

### 5.2.7 Antimalarial drug blood concentration

A total of 1 ml for determining the blood concentration of artesuante and dihydroartemisinin will be collected at according to the timetable below from an indwelling catheter. Specimens will be labelled anonymously (study number, day of follow-up, date). One ml of whole blood will be collected in appropriate collection tubes containing sodium fluoride/potassium oxalate as anticoagulant. The tubes will be pre-chilled on wet ice prior to use. After collection of blood, the tube should be placed on wet ice and processed as soon as possible after collection (the samples can be placed in the ice bath for 5 to 10 minutes prior to centrifugation to allow the blood to chill in the tube). Centrifuge blood within 15 minutes of collection. Centrifuge whole blood at (4°C) 2000 x g for 7 minutes to obtain plasma. Immediately after centrifugation, transfer plasma into a screw cap cryovial (Nalgene No.: 5000 0012 or suitable alternative) and freeze the plasma samples at or below - 80°C in a laboratory freezer until analysis at the ned of the clinical trial.The quantification of artesunate and dihydroartemisinin using LC-MS/MS and the pharmacokinetic analysis will be conducted at the clinical pharmacology laboratory of Mahidol Oxford Research Unit in Bangkok in Thailand. Samples will be batched and shipped for analysis upon completion of the study.

| Day | Hour | | | | | | | | | | |
| --- | --- | --- | --- | --- | --- | --- | --- | --- | --- | --- | --- |
| 0 | 0 | 0.25 | 0.5 | 0.75 | 1 | 1.25 | 1.5 | 3 | 4 | 6 | 8 |
| Volume of blood (ml) | 1 | 1 | 1 | 1 | 1 | 1 | 1 | 1 | 1 | 1 | 1 |

### 5.2.8 Pregnancy test

Female patients of child-bearing age, defined as those who menstruate and are aged > 18 years, will be asked to take a urine pregnancy test before enrolment in the study, because artesunate is contraindicated during the first trimester. They will also be asked to take a urine pregnancy test on day 28 or on early withdrawal from the study.

Female participants of child-bearing age, defined as those who menstruate and are aged > 18 years, and who are sexually active should use barrier contraceptive devices for the duration of the study. Condoms will be provided by the investigator or study team at the time informed consent is obtained, with appropriate counselling about the risks of becoming pregnant and exposing the fetus to the study medicines.

5.3 Safety assessment

Safety will be assessed by recording the nature and number of adverse events and serious adverse events. Adverse events will be assessed by direct questioning. An adverse event is defined as any unfavourable, unintended sign, symptom, syndrome or disease that develops or worsens with the use of a medicinal product, regardless of whether it is related to the medicinal product. All adverse events must be recorded on the case report form.

A serious adverse event is defined as any untoward medical occurrence that at any dose:

- results in death, is life threatening;
- requires hospitalization or prolongation of hospitalization;
- results in a persistent or significant disability or incapacity; or
- is a congenital anomaly or birth defect.

‘Life-threatening’ means that the person was at immediate risk for death; it does not refer to a adverse event that might have caused death if it were more severe. ‘Persistent or significant disability or incapacity’ means that a person’s ability to carry out normal life functions is substantially disrupted.

All serious adverse events occurring during the study must be recorded and reported by the principal investigator to the sponsor, regardless of whether the principal investigator considers the events to be related to the investigated medicine.

The investigator will collect information on all people who become pregnant while participating in this study and will record the information on the appropriate form. The person will also be followed to determine the outcome of the pregnancy. Generally, follow-up will be no longer than 6–8 weeks after the estimated delivery date. Any premature termination of pregnancy will be reported. While pregnancy itself is not considered an adverse event or a serious adverse event, any complication of pregnancy or elective termination for medical reasons will be recorded as an adverse event or a serious adverse event. A spontaneous abortion is always considered a serious adverse event and will be reported as such.

6. Study assessment

